#### Workplace culture

Workplace culture and management-level support is essential to the adoption of any individual-based intervention [27]. To facilitate the creation of a supportive workplace culture, senior and mid-level university managers were interviewed to ascertain their views on the study being conducted. Importantly, they were asked for input into the strategies that could be employed to communicate their support and encouragement to employees who chose to participate. Managers were highly supportive of the intervention being put in place with the caveat that guidelines/boundaries were put in place to sustain work productivity and limit distraction to others. Consequently, communications will be created for dissemination by senior management to employees that state that participation in the study will be supported and the direct managers will be encouraged to reiterate their support during weekly team meetings. Communications will also be sent to Heads of Department to explain that the study is running and to support the study messages in case any of their staff have opted to take part.

### Measures

#### Feasibility: recruitment, retention, and acceptability

Successful recruitment will be defined as recruiting at least 57 participants over 1 month. Successful retention will be deemed as retaining 80% of participants who complete pre-intervention measurements (T1 and 2) through to the measurements taken at post-intervention follow-up (T4).

At the end of the intervention period (T3), semi-structured interviews will be held with participants, managers, and where possible, those who did not participate in the intervention but were working in close proximity to those that were. The purpose of the interviews is threefold. First is to ascertain why participants volunteered and their experiences of participating in the Move More @ Work intervention. Here, we will examine perceptions of how the intervention was delivered by the coach, the usefulness of the behaviour change components included in the intervention and the extent to which a supportive culture was created with respect to taking opportunities to move. We will also examine the acceptability of the data collection processes (wearing the accelerometers, blood collection, etc.). Second is to examine the impact of the intervention of those who did not actively participate. Third is to identify managers’ perspectives of employee participation in the intervention and perceptions of its strengths and weaknesses. These data will inform subsequent changes to the recruitment into, and delivery of, the intervention in any future trial. Participants who drop out of the intervention will be followed-up where possible to ascertain reasons for dropping out.

### Pilot study outcomes

All measures (except blood-related measures) will be taken pre-intervention T1 and T2, end of the 12-week intervention (T3), and after a 12 week follow-up period (T4).

#### Change in physical activity behaviour

The number of opportunities to move that have been taken and 24 h patterns of physical activity will be identified using output from two accelerometers worn for 24 h a day for seven days at each assessment period. The ActiGraph Gt3x+ accelerometer is worn on an elasticated strap around the waist so that the accelerometer sits over the right hip (which provides accurate information about intensity of activity). The ActiGraph will be initialised to record activity at a sampling rate of 30 hz without the low-frequency extension. The ActivPAL3 is attached to the midpoint of the front of the right thigh with an adhesive dressing (which provides accurate information about posture). Prior to attachment, the ActivPAL will be inserted into nitrile two finger cots secured using a piece of adhesive to ensure it is water proof.

During each 7-day wear period, participants will complete a wear time diary, in which they will record times when either accelerometer was removed for more than 10 min (to identify non-wear time, e.g., for swimming or playing contact sport), times of day spent at work, and the time they attempted to fall asleep at night and got up in the morning.

ActiGraph data will be saved in 15-s epochs and data from both the ActiGraph and ActivPAL will be uploaded into Stata for processing. Non-wear time and hours spent at work will be identified based on times reported in the wear time diary. Days will only be considered valid if: wear time during waking hours is ≥ 10 h, and total wear time is ≥ 20 h. A participant’s data will only be included in analysis if it contains more than three workdays of valid data. Using the ActiGraph data, time spent sedentary will be classified as < 150 cpm using the *y*-axis [28]. Time spent in light and moderate-to-vigorous physical activity will be identified using a threshold of 150 to 1951 cpm and at least 1952, respectively, using the *y*-axis thresholds [29]. Time spent asleep will be identified using the Sadeh algorithm [30] constrained by the bedtimes reported in the wear time diary. The activPAL data will be used to identify time spend sitting, standing, and stepping that will be presented in parallel to the ActiGraph data. An opportunity to move will be defined as an increase in counts per minute to over 1000 cpm (ActiGraph data), when the participant is not seated (activPAL data) that is sustained for more than a minute (adjustments will be made if any participants have issues with mobility). Our previous work [31] indicates that the 1000 cpm threshold is associated with the intensity of activity shown in laboratory studies to produce clinically meaningful reductions in postprandial glucose and insulin concentrations. To avoid clusters of activity being identified as multiple breaks, at least 15 min of sedentary time must have been accumulated between opportunities to move. Total and work time spent in moderate-to-vigorous physical activity, light activity, sedentary behaviour, and sleep will be identified.

Self-reported adherence to the intervention will also be collected. Participants will record the number of opportunities to move taken each work day and will send the weekly record to the research team by email at the start of the following week.

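### Non-wear is taken from the diary with no device check named, so a long unlogged ActiGraph removal is kept as a valid, sedentary workday with few or no opportunities to move

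*Protocol article*

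**What the plan says.** All the rules sit in the protocol article under Change in physical activity behaviour.

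- **Source of non-wear.** "Non-wear time and hours spent at work will be identified based on times reported in the wear time diary". For the diary, "they will record times when either accelerometer was removed for more than 10 min". No rule based on runs of zero counts, or on disagreement between the two monitors, is named.
- **Valid day.** At least 10 h of wear while awake, "and total wear time is ≥ 20 h".
- **Minimum data.** "A participant’s data will only be included in analysis if it contains more than three workdays of valid data".
- **Scoring.** From the ActiGraph, "time spent sedentary will be classified as < 150 cpm". An opportunity to move needs more than 1000 cpm on the ActiGraph for over a minute while the activPAL shows the person is not seated. To keep clusters apart, "at least 15 min of sedentary time must have been accumulated between opportunities to move".
- **Devices.** The ActiGraph is on an elasticated waist strap. The activPAL is waterproofed and stuck to the thigh. Both are worn round the clock for seven days at each assessment.

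The primary outcome (Pilot study primary outcome) is the change in the average workday count. It is not expressed per hour of wear. The third progression criterion asks that at least half the sample average 8 or more at the end of the intervention.

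**The concern.** A belt that is off but not logged is treated as worn. Its zero counts fall below 150 cpm and are scored as sedentary. No opportunity to move can be detected, because detection needs more than 1000 cpm from that same device. The hours also count towards the 10 h and 20 h limits, so the valid-day rule passes the very day it is meant to reject.

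The count feeds the primary outcome, the within-person variability meant for planning later studies and, if it is judged on the accelerometer count, the progression threshold of 8. There is no control group (Study design and setting), so nothing offsets a difference in unlogged removal between the pre-intervention weeks and T3 or T4. Total and work sedentary time is inflated by any unlogged removal, short or long.

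**Working it through.** **1. The plan's own figure.** Inputs from Sample size: difference 3, SD 3, within-person correlation 0.5, power 90%, alpha 0.05 (two-sided assumed), cluster size 5, ICC 0.8.

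- SD of change = √(2 × 3² × (1 − 0.5)) = 3.
- n = (3 × (1.960 + 1.282) / 3)² = 10.51, rounded up to 11.
- Design effect = 1 + 4 × 0.8 = 4.2, and 11 × 4.2 = 46.2, rounded up to 47.

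The stated 47 reproduces and is not in dispute. Power at 47 is Φ(3 × √(47/4.2) / 3 − 1.960) = 92%.

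**2. When logging makes a difference.** The 20 h rule allows 24 − 20 = 4 h off. With 16 h awake (assumed), the waking rule allows 16 − 10 = 6 h, so the 20 h rule binds first. Take one opportunity per hour, an 8 h workday and five workdays, one of them with h hours of ActiGraph removal at work (all assumed). The true mean is 8.0. If the day is kept, the mean is (4 × 8 + 8 − h) / 5. If it is dropped, the mean is 8.0.

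| h | Mean, unlogged | Mean, logged | Due to missing log |
|---|---|---|---|
| 0.5 | 7.9 | 7.9 | 0 |
| 1 | 7.8 | 7.8 | 0 |
| 2 | 7.6 | 7.6 | 0 |
| 4 | 7.2 | 7.2 | 0 |
| 4.5 | 7.1 | 8.0 (day dropped) | 0.9 |
| 6 | 6.8 | 8.0 (day dropped) | 1.2 |
| 8 | 6.4 | 8.0 (day dropped) | 1.6 |

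Because the outcome is a raw count, the missing log has no effect here up to 4 h.

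**3. One full belt-off day in one person.** The observed mean is 8 × (d − 1)/d: 6.4 for d = 5 and 6.0 for d = 4. With four days, correct detection leaves three, and the rule of more than three valid workdays would exclude the record. With five days, a true mean of 8/(4/5) = 10 is needed to show 8, so anyone truly between 8 and 10 falls below the threshold.

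**4. Group level.** Assume true means of 5 before the intervention and 8 at T3, and let a share p of kept workdays be full unlogged removals. The observed change is 8(1 − p) − 5 if this occurs at T3 only, 3(1 − p) if equal in all periods, and 8 − 5(1 − p) if before the intervention only. Power uses the formula in step 1 with the SD held at 3.

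| p | T3 only (power) | Equal (power) | Pre only |
|---|---|---|---|
| 2% | 2.84 (89%) | 2.94 (91%) | 3.10 |
| 5% | 2.60 (83%) | 2.85 (89%) | 3.25 |
| 10% | 2.20 (69%) | 2.70 (85%) | 3.50 |
| 20% | 1.40 (34%) | 2.40 (76%) | 4.00 |

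No value of p can be taken from the documents.

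**The case against.** **The article may simply be silent.** It says non-wear is identified from diary times. It does not say that the signals go unexamined, and a processing manual may hold further rules. That is fair, but the article states a method, with cut-points and validity limits, and as stated it lets the long unlogged removal through. If a device check already exists, one sentence settles the matter.

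**Any unlogged removal might be thought to lower the count.** A reader might infer this, but step 2 shows otherwise: a logged removal that leaves the day valid lowers the raw count just as much. Nor is the direction always downward. Off-time scored as sedentary can satisfy the 15-minute separation rule and split one cluster of activity into two opportunities. If only the activPAL is off, the result depends on the posture it registers while loose.

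**Poor diaries in later weeks might be thought to bias the change downward.** The documents do not support this. They give no diary completion by time point. The same diary supplies the work times, so a neglected one tends to produce missing data. The problem needs work times that are filled in and a long removal that is left out. If that happens mainly before the intervention, the change is overstated.

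**A zero-count rule has its own bias.** Participants are selected for more than 5 h of sitting a day, and the intervention aims to break that up. A stand-alone rule could remove truly still sitting, more often before the intervention than after. This stands, and it limits the fix.

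**Self-report gives a partial check.** Weekly records during the intervention could reveal a false zero day, but they do not cover T1 or T2.

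**Conclusion.** The point holds in a limited form. Under the stated rules, an unlogged ActiGraph removal long enough to have invalidated the day if logged is kept as a valid workday with few or no opportunities to move. For one person, a full belt-off workday costs 1.6 on a true mean of 8 over five days. Over four days it costs 2.0 and retains a record that the protocol's own rule would exclude.

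At group level neither the size nor the direction is known. With 2% to 20% of kept workdays affected, a true change of 3.0 would appear as 2.84 to 1.40 if this occurs at T3 only, and as 3.10 to 4.00 if before the intervention only. These ranges rest on assumed shares, assumed means of 5 and 8, and full-day removals. They show sensitivity and do not predict what this trial will find. The effect on the progression threshold assumes that it is judged on the accelerometer count.

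**What to change.** Under Change in physical activity behaviour, keep the diary and add a pre-specified two-device check: any run of zero ActiGraph counts during waking hours in which the activPAL records sustained stepping is classed as ActiGraph non-wear. Fix in advance what counts as sustained stepping. Apply the valid-day rule after this step, in the same way at T1, T2, T3 and T4.

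Use a zero-run rule that does not require activPAL disagreement (for example 60 min) only as a sensitivity analysis, because it may remove truly still sitting.

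The cost is processing code. Both devices are already worn and their data are already loaded for processing. The check will not find periods when both devices are off, or when only the activPAL is off. A few more days or participants may become invalid, and a participant left without enough data at T1, T2 or T3 drops out of the primary analysis. Report the number of days and participants lost by time point.

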#### Pilot study primary outcome

The primary outcome is workday physical activity behaviour, specifically, the change in the mean number of opportunities to move taken during a workday from the pre-intervention period (T1 and T2) to the end of the intervention (T3) and post-intervention (T4) periods. An estimated change will be calculated, along with an estimate of the within-person variability, which can then be used in sample size calculations for future studies.

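### Workday validity for the work-hours primary outcome hinges on 20 h of total wear, so a fully recorded workday can be discarded and a half-recorded one kept

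*Protocol article*

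**What the plan says.** Under Pilot study primary outcome, the protocol article defines the outcome as "the change in the mean number of opportunities to move taken during a workday", from the pre-intervention period to T3 and T4.

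Under Change in physical activity behaviour:

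- Activity is recorded by "two accelerometers worn for 24 h a day for seven days at each assessment period". One device is removable: "The ActiGraph Gt3x+ accelerometer is worn on an elasticated strap around the waist". The other, the activPAL, is taped to the thigh and waterproofed.
- An opportunity to move needs both devices, because it is a rise in counts to "over 1000 cpm (ActiGraph data), when the participant is not seated (activPAL data) that is sustained for more than a minute".
- Work time is separately known: "Non-wear time and hours spent at work will be identified based on times reported in the wear time diary".
- One validity rule covers all accelerometer days. A day counts only if "wear time during waking hours is ≥ 10 h, and total wear time is ≥ 20 h".
- A minimum number of days follows: "A participant’s data will only be included in analysis if it contains more than three workdays of valid data".

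The Data analysis section then limits the primary analyses to participants with data at T1, T2 and T3.

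The article does not say whether total wear is judged on the ActiGraph, the activPAL or both. It also does not say whether a day runs from midnight to midnight, or when devices are fitted and removed.

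**The concern.** The 20 h threshold suits sleep and 24 h activity patterns, which the study also measures. It does not suit a count confined to work hours, because it lets wear at night decide whether a workday is used.

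The mismatch works in both directions. A complete workday can be rejected because of the night, and a day with much of its work time unrecorded can be accepted because the night was worn.

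Two further rules turn lost days into lost people: more than three valid workdays, and data at all three of the first time points. At stake are the number analysed for the primary outcome and how well the accepted days represent work time.

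**Working it through.** **1. The planned sample size, reproduced.** Inputs from the Sample size section: SD 3, within-person correlation 0.5, difference 3, 90% power, alpha 0.05 (taken as two-sided), design effect 4.2, dropout about 20%.

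- SD of change = 3 × √(2 × (1 − 0.5)) = 3.
- n = (1.960 + 1.282)² × (3/3)² = 10.51, rounded up to 11.
- Design effect = 1 + (5 − 1) × 0.8 = 4.2, and 11 × 4.2 = 46.2, rounded up to 47.
- 47 × 1.2 = 56.4, rounded up to 57.

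The stated 47 and 57 reproduce and are not in question here.

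**2. A complete workday that fails.** A total of 20 h allows at most 24 − 20 = 4 h of non-wear. Suppose the belt is off for sleep:

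- 7 h off: 24 − 7 = 17 h, fails.
- 8 h off: 24 − 8 = 16 h, fails.

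Waking wear is complete in both cases and exceeds 10 h. Only the 20 h condition rejects the day.

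**3. A half-recorded workday that passes.** Assume 8 h of sleep with the belt on and 4 h of belt removal at work:

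- Total wear = 24 − 4 = 20 h, passes.
- Waking wear = 24 − 8 − 4 = 12 h, passes.

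In an eight-hour workday, the length used in the progression criteria, half the work time is missing from the count.

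**4. Effect on the number analysed.** The article gives no night-removal rate, so a share s of habitual removers is assumed. They lose every workday. Remaining = 57 × (1 − s). Approximate power = Φ(√(n/4.2) − 1.96), since the difference equals the SD of change.

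| Assumed s | Remaining of 57 | Approximate power |
|---|---|---|
| 5% | 54 | 0.95 |
| 10% | 51 | 0.94 |
| 20% | 46 | 0.91 |
| 30% | 40 | 0.87 |

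This is before any other loss. If the planned 20% dropout also occurred, independently of belt removal, 57 × 0.8 × 0.9 = 41 would remain at s = 10% and 57 × 0.8 × 0.8 = 36 at s = 20%, both below 47.

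**5. Fitting and removal days.** If days are calendar days, a device fitted at 09:00 gives 24 − 9 = 15 h on the first day, and one removed at 09:00 gives 9 h on the last. Both fail. In general the fitting day fails if fitting is after 04:00, and the removal day fails if removal is before 20:00. With a weekday fitting and removal seven days later, a Monday-to-Friday worker has exactly four full workdays against a requirement of four. If days instead run from waking to waking (07:00 assumed), fitting at 09:00 gives 22 h and the day passes.

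**The case against.** The strongest reply is that participants are told to wear both devices day and night, so night removal departs from instructions. The diary's examples of removal are sport, not sleep. If the taped activPAL alone decided total wear, a belt left off at night would not matter. This is also a feasibility pilot that will ask about the acceptability of the accelerometers. All of this stands as a limit on size: the loss could be small, and the document does not let anyone estimate it. It does not rescue the rule for a work-hours outcome. The waist device supplies the counts that define that outcome, and the diary covers removal of either device. The self-reported counts described are weekly records kept during the intervention, so they cannot replace the change from T1 and T2.

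It could also be said that processing detail belongs in a fuller document. But the article does state a rule, and the rule as stated fits the outcome badly.

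Three stronger readings are tempting and are not supported:

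- *Fitting and removal days can never count.* This needs calendar days and daytime visits, and the article fixes neither.
- *Most of the sample would be lost.* With four countable days and an assumed independent 10% daily failure, 0.9⁴ = 0.656 qualify per wave and 0.656³ = 0.28 at all three. That depends on the unstated four-day condition. It also depends on independent failures, which is not how habitual night removal behaves. With five countable days the same 10% gives 0.78.
- *The result is biased toward compliant people.* Nothing in the article links night removal to adherence, and the outcome is a within-person change. Exclusions could limit generalisability, but no direction of bias is shown.

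**Conclusion.** The point holds as a poorly fitted validity rule, not as an error in the sample size. If total wear is judged on the ActiGraph or on both devices, the rule discards workdays that are complete for the primary outcome when the belt is off for more than 4 h at night. It can also admit days with 4 h of work time missing.

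The size is unknown. With 10–20% habitual night removers, 51 to 46 of 57 remain and power stays at about 0.94 to 0.91 if nobody else is lost. The loss becomes material when it adds to ordinary dropout. The lack of spare workdays for a Monday-to-Friday worker is conditional on calendar days and on weekday fitting and removal in working hours. This is a cheap improvement worth making, not a threat to the study.

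**What to change.** For work-time outcomes, define a valid workday as one on which both devices were worn for a prespecified share of diary-reported work hours, regardless of night or total wear. A share of 80% is an example; the article offers no basis for a particular figure. Keep the 10 h waking and 20 h total conditions for the 24 h activity and sleep outcomes. State the day boundary and which device decides wear under each rule, before the data are processed.

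The cost is one sentence and one flag in the processing code, with no new data. The downside is two valid-day definitions, so the analysed samples may differ between work-time and 24 h outcomes.

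The change leaves the four-day minimum and the three-wave requirement as they are, and it does not always recover fitting and removal days. With assumed work hours of 09:00–17:00 and a noon visit, those days have 5/8 (63%) and 3/8 (38%) of work time and would fail an 80% rule.

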### Participant inclusion and exclusion criteria

Participants will be drawn from academic, professional and administrative employees at the University of Otago. To be eligible for inclusion, participants must (1) be older than 18 years; (2) self-report spending > 5 h per day, on at least 3 days of the week in a seated position at work (objectively measured sedentary time of participants who self-report being sedentary at work, has been reported to be 5.5 h [5]); and (3) not use a sit-to-stand desk. Part-time employees are eligible providing they meet the criteria above. Participants will be excluded from participating if (1) they have any physical or physiological impediments to participating in physical activity because this study requires participants to undertake short bouts of physical activity (all participants will be screened for contra-indications using the Physical Activity Readiness Questionnaire [PAR-Q] [24] prior to starting the study), (2) they have a planned absence from work for > 2 weeks during the intervention period, or (3) they plan to relocate to another workplace other than the University of Otago, Dunedin campus, during the 6 month study period (intervention and follow-up). Participants will also be excluded from participation if they are pregnant, as pregnancy has the potential to affect waist circumference, and other components of the cardio-metabolic risk score (a secondary outcome measure).

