### Data analysis

Descriptive statistics will be used to assess the feasibility outcomes of time taken to recruit and retention of participants across the intervention. Intervention acceptability will be assessed through analysis of participant interviews. They will be open-coded, examining for common themes in relation to acceptability and usefulness of the intervention. They will then be axially coded, investigating the relationships between the themes and the similarities and differences in individuals’ reporting and experiences of those themes [39].

The primary and secondary outcomes of the pilot study will be assessed using mixed effects regression models, where the independent variables in the model will be: time since baseline, pre-/post-intervention (dummy variable), and a time by pre-/post-intervention interaction variable. The immediate effect of the intervention will be represented by the regression coefficient of the pre-/post-intervention variable, with the regression coefficient of the interaction term representing the difference in change in the outcome over time. Because this study examines within-person changes, only participants with data at T1, T2, and T3 will be included in the primary analyses, using an intention-to-treat approach. Office clusters will be included as a random effect. Where appropriate, the Stata command ‘itsa’ (for interrupted time series analysis) will be used. Mean changes in outcomes with 95% CI will be reported. To illustrate the results of the pilot study and assist in interpretation, line graphs will be generated. No interim analysis is planned for the trial. All quantitative statistical analysis will be carried out using Stata (StataCorp, Texas).

To estimate sample sizes for a future effectiveness trial, standard deviations of the change in health outcomes (e.g., body weight, blood pressure, and lipids) between T2 and T3 will be calculated. Estimates of intraclass correlation coefficients (from office clusters) will also be used to estimate the design effect if the future trial is planned to be a cluster randomised controlled trial [40].

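### The minimum of four valid workdays in a seven-day wear period shuts three-day-a-week staff, whom the trial admits, out of the primary analysis

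*Protocol article*

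**What the plan says.** All references are to the protocol article.

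- **Participant inclusion and exclusion criteria.** Participants must "self-report spending > 5 h per day, on at least 3 days of the week in a seated position at work". The section adds: "Part-time employees are eligible providing they meet the criteria above".
- **Change in physical activity behaviour.** The outcome comes from "two accelerometers worn for 24 h a day for seven days at each assessment period". A day counts as valid with at least 10 h of wear while awake and at least 20 h overall. On that basis, a person's "data will only be included in analysis if it contains more than three workdays of valid data".
- **Data analysis.** For the pilot outcomes, "only participants with data at T1, T2, and T3 will be included in the primary analyses".
- **Pilot study primary outcome.** The outcome is the change, from T1 and T2 to T3 and T4, in the average count of opportunities to move per workday. It depends on the accelerometer data that the valid-day rule filters.
- **Sample size.** 47 participants are needed and 57 will be recruited. The difference is attributed to drop-out of about 20%. Loss through invalid wear is not mentioned.

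The article contains no exemption from the valid-day rule for part-time staff and no longer wear period for them.

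**The concern.** The eligibility floor is three days a week and the analysis floor is four valid workdays in a week. Someone employed for exactly three days can be recruited, coached and measured, yet cannot contribute to the primary outcome. A four-day worker can contribute only with no invalid workday in any of the three required waves.

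Three things are at stake.

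- **Selection by contract.** Exclusion depends on contracted days, a baseline characteristic, and not only on compliance. That sits badly with the intention-to-treat approach named under Data analysis, and it limits what the pilot can say about part-time staff.
- **Feasibility counts that diverge from the analysable sample.** Three-day staff count towards the recruitment target of 57 and, if they attend, towards 80% retention. Both targets could be met while the analysable sample falls short.
- **Progression criterion 3.** This asks whether at least half of the sample averaged 8 or more opportunities to move. If it is judged on accelerometer data, three-day staff have no usable value.

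**Working it through.** **Inputs from the protocol.** Minimum valid workdays: more than three, so 4. Wear period: 7 days per assessment. Assessments required: T1, T2 and T3. Sample size inputs: SD 3, within-person correlation 0.5, difference 3, power 90%, alpha 0.05 (taken as two-sided), cluster size 5, ICC 0.8, drop-out about 20%.

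**Assumptions.** The probability p that a scheduled workday is valid is not given, so 0.90, 0.95 and 0.98 are shown. Days are first treated as independent. The rule is read as applying per assessment, which is the natural reading because wear is set per assessment and data are needed at each time point.

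**1. The plan's own figure.** SD of change = 3 × √(2 × (1 − 0.5)) = 3. n = ((1.960 + 1.282) × 3/3)² = 10.51, rounded up to 11. Design effect = 1 + (5 − 1) × 0.8 = 4.2. 11 × 4.2 = 46.2, rounded up to 47. 47 × 1.2 = 56.4, rounded up to 57. Both stated figures are reproduced, and the step from 47 to 57 is used up by drop-out.

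**2. Three-day workers.** There are at most 3 workdays in any 7 days, so P(at least 4 valid) = 0 for every p, including p = 1. This step does not depend on p or on independence.

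**3. Four-day workers.** All four workdays must be valid in each wave. The probability is p⁴ per wave and p¹² over three waves.

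**4. Five-day workers.** One invalid workday per wave is tolerated. The probability is 5p⁴(1 − p) + p⁵ per wave, cubed over three waves. At p = 0.90 this is 0.32805 + 0.59049 = 0.91854, and 0.91854³ = 0.775 (0.77499 before rounding, so 77%).

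Share analysable over T1 to T3, before drop-out:

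| p | Three-day: ≥4 rule | Three-day: ≥3 rule | Four-day: ≥4 rule | Four-day: ≥3 rule | Five-day: ≥4 rule | Five-day: ≥3 rule |
|---|---|---|---|---|---|---|
| 0.90 | 0% | 39% | 28% | 85% | 77% | 97% |
| 0.95 | 0% | 63% | 54% | 96% | 93% | 99.7% |
| 0.98 | 0% | 83% | 79% | 99% | 99% | 100% (rounded) |

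The ≥3 columns use p⁹ for three-day workers and the corresponding binomial tails, cubed, for the others.

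**5. Dependence between days.** If people differ in compliance around a mean of 0.90, the average of p¹² is at least 0.90¹², so 28% is the floor for four-day workers at that mean. With beta-distributed compliance and within-person correlation of 0.1 to 0.3 (illustrative), 44% to 62% of four-day workers remain. The five-day figure hardly moves, at 76% to 78%.

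**6. Illustration of power.** Power = Φ(√(N/4.2) − 1.96), since difference/SD of change = 1. After 20% drop-out, 57 × 0.8 = 45.6 remain, with power 90.9%. The staff mixes below are assumed.

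- Losing only three-day staff at 5%, 10% or 20% of the sample leaves 43.3, 41.0 or 36.5, with power 89.5%, 87.8% or 83.8%.
- With 10% three-day and 10% four-day staff and independent days, p = 0.90 leaves 29.6 (75.6%) and p = 0.95 leaves 36.5 (83.9%).

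**The case against.** The strongest reply accepts the mismatch and disputes its size.

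- **The affected group may be small.** The three-day criterion counts days of long sitting, not days worked. A full-time employee who sits for more than 5 h on only three days is eligible, has five workdays and can reach four valid ones, because the valid-day rule does not require high-sitting days. This stands. Certain exclusion is confined to people employed for three days, and the protocol does not say how many there will be.
- **Compliance may be high.** Wear is round the clock, the thigh device is waterproofed and stuck on, and up to 4 h of non-wear a day is tolerated. Validity above 0.90 is plausible, and with perfect wear four- and five-day staff lose nobody. This also stands, but it does not help three-day staff.
- **It is a feasibility pilot.** Recruitment, retention, interviews, questionnaires, the risk score and self-reported adherence do not depend on valid accelerometer days. That lowers the severity but leaves the stated primary pilot outcome exposed.
- **The rule does not say that it applies per assessment.** Pooling days across assessments would rescue three-day staff, but it fits poorly with an analysis that needs data at each of three time points.

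Two stronger readings are tempting. A reader might infer that losses will exceed the 20% allowed. The protocol gives neither the part-time share nor the wear compliance, so this cannot be derived: five-day staff alone would lose about 23% at p = 0.90, 7% at 0.95 and 1% at 0.98. A reader might also infer that the estimate will describe only near-full-time, highly compliant staff. That goes too far, because five-day staff may lose one workday in every wave and still count.

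**Conclusion.** The point holds as a conflict between two stated rules. Detail left to an analysis plan is not the issue. Exclusion of people employed three days a week is certain and needs only the per-assessment reading. Four-day staff have no margin for a single invalid workday. How many are lost depends on assumed validity: 28%, 54% or 79% remain at 0.90, 0.95 or 0.98 under independence, and more than that if compliance clusters within people. The overall loss and its effect on power are unknown from the document. The main harm is selective exclusion of part-time staff from the primary outcome, and possibly from progression criterion 3. Severity: should-fix.

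**What to change.** Reconcile the eligibility criteria with the valid-day rule by requiring at least three valid workdays per assessment, stated as applying at each of T1, T2, T3 and T4. Keep the four-day rule as a sensitivity analysis.

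The cost is one changed threshold, one additional analysis, and slightly noisier means for participants who contribute only three days. Three-day staff would then be able to enter, though only with every workday valid (39% over T1 to T3 at p = 0.90 under independence). A lower minimum for those staff, or weighting by the number of valid days, would ease this further. Both are optional and go beyond what the inconsistency requires.
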